**Figure 1 figure1:**
[figure not shown]
Study design.

### Data Collection

#### Clinical Data

##### Demographics and Disease Characteristics

Demographic data and cancer characteristics (localized or biologically relapsed prostate cancer, stage of disease, radiation regimen, concomitant treatments, and comorbidities) of the patients will be collected.

##### Clinical Examination

Clinical examination at each visit will include performance index (performance status), weight, blood pressure, heart rate, and oxygen saturation. 

##### Monitoring of Radiotherapy Adverse Events and Patient-Reported Quality of Life Using the Cureety Platform

The Cureety platform will allow remote monitoring of urinary symptoms reported by patients in accordance with the CTCAE (Common Terminology Criteria for Adverse Events) guidelines [22] (Multimedia Appendix 1). 

Patients will complete the Pelvic Radiation Adverse Events Questionnaire at the inclusion visit, then once a week for 3 months (weeks 1 to 12), and then at the end-of-study visit (week 52). The questionnaire includes the following items: fatigue, nausea or vomiting, pain, hematuria, frequency of urination (pollakiuria), urinary burning, diarrhea, fecal incontinence, urinary leakage, blood in the stool (rectorrhagia), constipation, weight loss, and dysuria.

On receipt of the questionnaires on the adverse effects of radiation, an artificial intelligence algorithm will classify patients into 1 of 4 states: correct condition (green), fragile state (yellow), condition to monitor (orange), and critical condition (red; Figure 2). The patient will receive therapeutic advice depending on the severity of the symptoms. If the patient’s condition changes to orange (watch) or red (critical), rapid management of the patient will be activated by the health care team (Figure 2).

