**Methods:**

Patients with intermediate-risk localized prostate cancer who are eligible for localized radiotherapy will be included. Inflammatory biomarkers will be analyzed in urine and blood samples before the start of radiotherapy and at weeks 4, 12, and 48 of irradiation, through quantitative methods such as a multiplex Luminex assay, flow cytometry, and enzyme-linked immunosorbent assay. We will also characterize the patients’ gut and urine microbiota composition using 16S ribosomal RNA sequencing technology. Between sample collection visits, patients will complete various questionnaires related to radiation cystitis symptoms (using the International Prostate Symptom Score), adverse events, and quality of life (using the Functional Assessment of Cancer Therapy–Prostate questionnaire), using the Cureety digital remote monitoring platform. Upon receipt of the questionnaires, an algorithm will process the information and classify patients in accordance with the severity of symptoms and adverse events reported on the basis of Common Terminology Criteria for Adverse Events and International Prostate Symptom Score standards. This will allow us to correlate levels of urinary, blood, and fecal biomarkers with the severity of acute radiation cystitis symptoms and patient-reported quality of life.

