## Appendix

Multimedia Appendix 1 The Common Terminology Criteria for Adverse Events (version 5.0) questionnaire for classification of noninfectious cystitis and the International Prostate Symptom Score for the severity of prostate cancer symptoms.

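### The article gives several sources for cystitis severity, one of them built on mostly non-urinary symptoms, and takes none relative to the inclusion value

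*Protocol article*

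**What the plan says.** Four places in the protocol article bear on how cystitis severity is measured.

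- **Abstract, Methods.** After the questionnaires arrive, "an algorithm will process the information and classify patients in accordance with the severity of symptoms and adverse events reported", using CTCAE and IPSS standards. The next sentence draws the link to the analysis: "This will allow us to correlate levels of urinary, blood, and fecal biomarkers with the severity of acute radiation cystitis symptoms".
- **Monitoring of Radiotherapy Adverse Events (Cureety platform).** "The questionnaire includes the following items: fatigue, nausea or vomiting, pain, hematuria, frequency of urination (pollakiuria), urinary burning, diarrhea, fecal incontinence", and the list ends with "urinary leakage, blood in the stool (rectorrhagia), constipation, weight loss, and dysuria". From this questionnaire "an artificial intelligence algorithm will classify patients into 1 of 4 states", green to red. The stated use is care: for the two worst states, "rapid management of the patient will be activated by the health care team". The questionnaire is completed at inclusion, weekly in weeks 1 to 12, and at week 52.
- **End Points and Evaluation.** Symptoms and severity of early cystitis come from patient-reported CTCAE self-assessment at inclusion and weekly in weeks 1 to 12. IPSS covers voiding disorders at inclusion and weeks 4 and 12. No algorithm is mentioned.
- **Appendix.** It names a CTCAE version 5.0 "questionnaire for classification of noninfectious cystitis", together with the IPSS, which it describes as grading prostate cancer symptoms.

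The exclusion criteria cover certain urinary tract operations, bladder or urethral cancer, a history of cancer, and earlier pelvic irradiation. They set no limit on voiding symptoms at entry. The statistical section plans on 60 men, 30 with cystitis and 30 without.

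**The concern.** The split into men with and without cystitis, and the severity ranking within it, form one side of every planned marker correlation. If that side is not specific to the bladder, three things can go wrong.

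- A man with diarrhoea or fatigue could be placed in a worse class without having cystitis, which dilutes the contrast.
- Bowel symptoms entering the severity measure could produce an association with fecal markers or fecal microbiota that is then reported as a bladder finding. A secondary objective relates the fecal microbiota to cystitis severity, so this analysis is planned.
- The article lists frequency, urgency and difficulty in urinating among the early signs of radiation cystitis. A man who has these before irradiation would count as a case unless his inclusion value is taken into account.

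Leaving several candidate definitions open also allows the choice to be made after 33 markers have been seen.

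**Working it through.** **1. Item count.** Sorting the 13 questionnaire items:

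| Group | Items | Count |
|---|---|---|
| Clearly urinary | hematuria, frequency, burning, leakage, dysuria | 5 |
| Bowel or general | fatigue, nausea or vomiting, diarrhoea, fecal incontinence, rectal bleeding, constipation, weight loss | 7 |
| Ambiguous | pain | 1 |

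Urinary share: 5/13 = 38%. Non-urinary share: 8/13 = 62%, or 7/13 = 54% if pain is assigned to the bladder. Most items are non-urinary either way.

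**2. Do the sections name the same variable?** The abstract uses an algorithm classification, and the only algorithm output the article describes is the four-state one. The end point section uses patient-reported CTCAE questionnaires on a weekly schedule. The only weekly instrument described is the 13-item questionnaire, so the end point probably rests on the same items, but no rule says which items or how they are combined. The appendix grade is specific to the bladder, but no section assigns it to an analysis. IPSS is not among the 13 items and is completed only at visits, yet the abstract counts it among the standards behind the classification. These descriptions do not fix one variable.

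**3. Baseline.** Both the questionnaire and IPSS are completed at inclusion. No section states a difference from, or adjustment for, the inclusion value when cystitis or its severity is defined.

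**4. The plan's own figure.** 60 × 0.5 = 30 with cystitis and 30 without, which reproduces the stated split. The total of 60 cannot be re-derived: the article says it has no statistical basis and gives no effect size or SD.

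**5. Illustration of dilution.** From the article: 30 v 30, two-sided alpha 5%, power 80%. Assumed: one marker, no multiplicity correction, a two-sample t test, all 30 true cases labelled correctly, and a share f of the 30 non-cases labelled as cases.

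- Difference detectable with 80% power at 30 v 30: 0.736 SD.
- Labelled groups: n1 = 30 + 30f and n0 = 30 − 30f.
- Observed difference: 0.736 × 30/(30 + 30f) = 0.736/(1 + f).
- Noncentrality: observed difference divided by √(1/n1 + 1/n0).

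| f | Labelled groups | Non-cases among labelled cases | Observed difference (SD) | Power |
|---|---|---|---|---|
| 0 | 30 v 30 | 0% | 0.736 | 80% |
| 10% | 33 v 27 | 9% | 0.669 | 72% |
| 20% | 36 v 24 | 17% | 0.613 | 63% |
| 40% | 42 v 18 | 29% | 0.526 | 45% |

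For f = 20%, √(1/36 + 1/24) = 0.264 and 0.613/0.264 ≈ 2.33, giving 63%. For f = 40%, √(1/42 + 1/18) = 0.282 and 0.526/0.282 ≈ 1.87, giving 45%. The calculation ignores the small extra variance from mixing cases and non-cases in one group.

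**The case against.** The strongest reply is that the article never says markers are correlated with the colour state. The data collection section uses the colours for advice and for activating care, the end point section relies on CTCAE self-assessment, and the appendix points to a bladder-specific grade. The abstract's classification also draws on IPSS, so it is not simply a score over the 13 items. Neither the weighting nor the relevant figure is shown, and an item count says nothing about weights. Handling of baseline is often left to the SAP or full protocol.

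Much of this stands. A reader might infer that severity *is* the colour state and that the markers *will* be correlated with general pelvic toxicity. The documents do not support that; contamination is a risk that the text leaves open. Nor does silence in a condensed article show that baseline will be ignored.

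A reader might also infer that urinary infections will be counted as radiation effects and distort the urinary cytokines. The documents give no basis for the cytokine claim, and how infection is ruled out may be set out in material not shown.

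What the reply does not remove is the text itself. The abstract names the algorithm's classification as the route to the correlation, other sections name different sources, and nothing chooses among them.

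**Conclusion.** The point holds as an inconsistency in the outcome definition that carries a foreseeable bias. The article offers an algorithm classification, patient-reported CTCAE self-assessment and a CTCAE noninfectious-cystitis grade as sources of severity, and states none of them relative to inclusion. Markers may be correlated partly with bowel or general toxicity and with voiding symptoms present before irradiation.

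The size is unknown. The fall in power from 80% to about 63-45% depends on an assumed mislabelling rate of 20-40%, on an effect size back-solved from 30 v 30, and on a two-group comparison of a single marker. It shows how sensitive the design is and is not an estimate of what will happen. The matter should be settled before marker data are analysed.

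**What to change.** For all biomarker and microbiota analyses, name one bladder-specific severity variable and use it throughout.

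- Choose either the CTCAE noninfectious-cystitis grade or the worst grade over the urinary items (hematuria, frequency, burning, leakage, dysuria). The article lists pain as an early symptom, so include bladder pain if the questionnaire item can identify it, and give the reason if it is left out.
- Count it as worsening over the inclusion grade and analyse it as ordinal.
- Analyse IPSS separately, as change from inclusion or adjusted for inclusion IPSS. It is completed only at visits and is not graded like the weekly items, so the two should not be merged.
- Do not use the four-colour state as an analysis outcome, and align the abstract with the end point section accordingly.
- Exclude samples taken during urinary infection or antibiotic treatment only as a sensitivity analysis, and only if these events are in fact recorded during follow-up. The article lists concomitant treatments without saying when they are collected.

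The cost is an outcome definition in the SAP and a clarified sentence in the protocol. The questionnaire and IPSS are already scheduled at inclusion and during follow-up, so no extra visit or sample is needed. The downside is somewhat fewer men counted as cases.

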**Figure 2 figure2:**
[figure not shown]
Monitoring of radiotherapy adverse events and patient-reported quality of life using the Cureety app.

##### International Prostate Symptom Score

The International Prostate Symptom Score (IPSS) [23] is a structured, validated, self-administered questionnaire that assesses lower urinary tract voiding disorders. The questions cover the following items: incomplete emptying of the bladder, frequency of micturition, intermittent micturition (stopping and restarting the stream), urgent micturition (feeling of “urgency”), weak stream, effort to urinate (forcing or pushing), and nocturia (Multimedia Appendix 1).

##### The Functional Assessment of Cancer Therapy–Prostate Questionnaire

The Functional Assessment of Cancer Therapy–Prostate (FACT-P) questionnaire [24] is a prostate cancer–specific, self-administered questionnaire that assesses weight loss, appetite, pain, physical comfort, urinary, and sexual and bowel function in 12 items. The score ranges from 0 to 156, with higher scores reflecting a better quality of life.

##### The International Physical Activity Questionnaire

The International Physical Activity Questionnaire (IPAQ) [25] is a 7-item questionnaire that assesses overall physical activity and sedentary time over the past 7 days. The questionnaire assesses intense or moderate walking activity, as well as time spent sitting (sedentary), whether during leisure activities, at work, in daily life, or during transport. The questionnaire classifies the subject in accordance with 3 levels of activity: inactive, moderate, and high [25].

The IPSS, FACT-P and IPAQ questionnaires will be completed by the patient via the Cureety platform at inclusion and at the visits at weeks 4, 12, and 52.

### Biological Data

#### Overview

Nearly 2 dozen studies have defined urinary biomarkers indicative of visceral disorders. Three main categories of markers have been studied: proteins involved in epithelial cell growth, mediators of inflammation, and neurotrophins. All marker levels were significantly altered in patients with interstitial cystitis, but antiproliferative factor, epidermal growth factor, and heparin-binding epidermal growth factor were the markers with the most promising results [26,27]. For radiation cystitis, the 2 studies by Zwaans et al [9,28] are the only ones to report elevated urinary levels of plasminogen activator inhibitor 1, the matrix metalloproteinases tissue inhibitor of matrix metalloproteinase 1 and 2, hepatocyte growth factor, VEGF-A, and placental growth factor. Based on the biomarkers reported in the literature, we chose to assess variations in the expression of 33 serum and urine biomarkers [9,28].

Biomarkers of urinary and intestinal microbiota may be prognostic of radiation-induced functional disorders [18-20]. Thus, we chose to assess changes in the composition of the urinary and fecal microbiota before, during, and after radiotherapy.

Physical activity, as determined on the basis of muscle contraction and the oxygen consumption it generates, can induce changes in the gut microbiota profile, helping to explain the health benefits of exercise. Researchers have identified differences in the composition of the gut microbiota of elite athletes in comparison with those of sedentary individuals [29]. A recent study has shown that the composition of the microbiota also differs in accordance with the sport practiced [30].

The collected samples will be analyzed for circulating biomarkers and microbiota composition.

#### Inflammatory and Remodeling Biomarkers

Overall, 6 mL of blood and 5 mL of urine per patient per visit will be used for the analysis of the following 33 biomarkers: inflammatory biomarkers (including macrophage migration inhibitory factor; cytokines IL-1α, IL-1β, IL-4, IL-6, IL-7, IL-8, IL-10, IL-13, and IL-17α; macrophagic inflammatory protein 1α; TNF-α; vascular cell adhesion molecule 1; intercellular adhesion molecule 1; chemotactic cytokines including monocyte chemoattractant protein 1 and 3 and regulated on activation, normal T-expressed, and secreted; the C-X-C motif chemokine ligand 10; the M1:M2 macrophage ratio; CD4^+^ and CD8^+^ T cells; and CRP) and biomarkers of remodeling (including plasminogen activator inhibitor 1, metalloproteinases such as matrix metalloproteinase 9, matrix metalloproteinase inhibitors including tissue inhibitor of matrix metalloproteinase 1 and 2, hepatocyte growth factor, placental growth factor, VEGF, epidermal growth factor, heparin-binding epidermal growth factor, nerve tissue growth factor, and glycoprotein GP51).

#### Urinary and Fecal Microbiota

The advent of molecular biology and high-throughput sequencing has revealed the diversity of urinary and fecal microbiota and led to a better understanding of these ecosystems. Over the past 2 decades, shotgun metagenomic and 16S ribosomal RNA sequencing approaches have been widely used to determine the composition of these microbiota.

#### Lipidome and Metabolome

This involves the analysis of metabolites (small molecules) and lipids in the blood and urine before, during, and after radiation therapy. The identity and quantity of the different metabolites and lipids depend on several factors such as available nutrients, environmental stimuli, or physiological state. Metabolome and lipidome analyses help elucidate the influence of radiotherapy on the expressed phenotype and metabolism of the patient. A GC 7890B gas chromatography system (Agilent) coupled to a MS 7010 triple quadrupole mass spectrometer will help identify lipid and metabolic proinflammatory mediator profiles in the serum and urine of patients.

### Statistical Analysis

As this is a pilot exploratory study, the sample size was not based on a statistical argument. As the variability and evolution of biomarkers over time and the history of the disease are not known, and in order to explore the links between biomarkers and the occurrence of radiation cystitis, based on the hypothesis that half of the patients initially included will develop cystitis, a sample size of 60 individuals—including 30 individuals with cystitis and 30 individuals without cystitis—seems acceptable. Statistical analysis will be carried out using SAS (version 9.4; SAS Institute Inc) and R (The R Foundation) [31].

Basic statistics will be used for continuous variables n, missing n (if applicable), mean, type of deviation, median, first and third quartiles, and minimum and maximum values, and for categorical variables, we will use frequency and percentage values.

The type I error (α, 2-sided) will be 5%. The type II error (β) will be 20%; that is, a power (1-β) of 80% will be considered.

### End Points and Evaluation

The primary end point will indicate variations in the expression of the 33 inflammatory and remodeling biomarkers assessed using the MILLIPLEX MAP technique for the analysis of circulating markers and flow cytometry for the analysis of the immune population at the 4th and 12th weeks after the start of irradiation. 

The secondary endpoints will indicate symptoms and the severity of early radiation cystitis through electronic reporting of patient-reported outcomes–CTCAE self-assessment questionnaires at inclusion and once a week during weeks 1 to 12. We will also be interested in voiding disorders, quality of life, and physical activity assessed using the IPSS, FACT-P, and IPAQ self-assessment questionnaires at inclusion and at weeks 4 and 12. Furthermore, we will characterize the composition of the urinary and fecal microbiota via 16S ribosomal RNA sequencing at baseline and at weeks 4 and 12.

Finally, we shall explore the eligibility criteria, and then at week 52, the symptoms and severity of cystitis will be assessed through electronic reporting of patient-reported outcomes–CTCAE self-assessment questionnaires, and voiding disorders, quality of life, and physical activity will be assessed with the IPSS, FACT-P, and IPAQ self-assessment questionnaires, and then the composition of the urinary and fecal microbiota will be characterized through 16S ribosomal RNA sequencing. We will analyze serum and urine lipidome and metabolomes at weeks 4, 12, and 52.

## Results

The RAABIO study started in March 2022. It is an original study combining digital data collection to monitor patients' symptoms and biological markers during irradiation. We estimate a recruitment period of approximately 18 months. The final results are expected in 2024.

## Discussion

The quality of life of long-surviving patients is a goal of their care. Minimizing the impact of our treatments remains very challenging. This study is expected to improve our knowledge of the pathophysiology of radiation cystitis and its impact on the quality of life of our patients.

Radiation cystitis—which is characterized by hematuria, inflammation, and partly by fibrosis—has a strong impact on the daily life of our patients. Telemonitoring allows the recording of patients' experiences and the assessment of the impact of side effects on his quality of life. Collecting data from the patient (patient-reported outcomes) help to correct the discrepancy in the severity of the side effects when reported by the clinician or by the patient. Remote monitoring has been shown to provide high-quality care and has the potential to significantly improve patient care.

An increasing number of pathologies or their treatments, including radiation therapy of the prostate, now report alterations of the host-microbiome symbiosis [32,33]. In addition to remote monitoring patients’ experiences, disorders involving the gastrointestinal area could be assessed by monitoring host-microbiome interactions using wireless ingestible capsules technologies as described recently by Miley et al [34]. These emerging technologies could be useful in tailoring daily treatments and helping patients reduce the side effects of radiation.

This prospective study is the first to explore the overexpression of inflammatory proteins in fluid biopsies from patients with symptoms of acute radiation cystitis. In addition, the 1-year follow-up after treatment will allow us to predict which patients are at risk of late radiation cystitis and to guide them toward radioprotective treatment. The RABBIO study will provide a better understanding of the pathophysiology of radiation-induced cystitis, along with data on the kinetics of these biomarkers. The results of this study will allow us to develop strategies to limit radiation damage to the bladder and improve the quality of life of patients.

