Early symptoms of radiation cystitis may occur during treatment and up to 3 months after the end of radiotherapy, with an estimated all grade incidence of nearly 50% after pelvic irradiation [5]. These side effects are characterized by frequent and urgent urination during day- and nighttime, a burning sensation during urination (irritative symptoms), and pain. Difficulty in urinating (obstructive symptoms) or, more rarely, blood in the urine (hematuria) may also be present [6]. More rarely, in 5%-10% of cases, complications appear later (more than 6 months after radiotherapy), whether or not they were preceded by early signs [5,7]. Late lesions involve blood vessel damage and fibrosis of the bladder wall, which may progress chronically and lead to bladder atrophy and even retraction in the most extreme cases [5]. Clinical signs vary depending on the dominant clinical form: cystalgia, pollakiuria, bladder hyperactivity, and isolated mictional disorders. In a classic clinical scenario, recurrent hematuria is a predominant symptom, occurring in abundance and with variable frequency, which can potentially progress to urinary retention with bladder clotting. The chronic and recurrent nature of hemorrhagic cystitis often has a considerable impact on the quality of life of patients. The most severe forms can lead to clot formation and acute urinary retention, which can be life threatening [5,7].

Although some factors have been identified, such as the dose received, fractionation and, comorbidities (eg, diabetes and tobacco smoking), the pathophysiology of radiation cystitis remains poorly studied, particularly because of the risks of complications arising from access to the bladder tissue post irradiation, thus limiting our knowledge of and therapies targeting this process*.*

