### Participants’ Calendar

Early symptoms of radiation cystitis are likely to occur during treatment or within 3 months of radiotherapy in approximately half of the patients [7]. Therefore, we decided to follow the early manifestations of radiation-induced bladder toxicity for 3 months (weeks 1 to 12) and to attempt to identify biomarkers that are potentially related to acute radiation cystitis symptomatology.

Late manifestations of bladder damage secondary to pelvic irradiation may occur after a minimum of 3 months or even several years after the end of irradiation [4,6]. It has been established that the average delay in the occurrence of these complications is 2 years [6]. However, the pathophysiological changes between the end of radiation and the occurrence of late complications are not known. In this study, we aim to, as an exploratory objective, determine biomarkers that may be predictive of late radiation cystitis by quantifying biomarkers at week 52.

The design of RABBIO study is shown in Figure 1.

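### The stated ability to predict late radiation cystitis and steer treatment from 1-year follow-up is not supported by the plan's own figures of 60 patients, a 5%-10% late rate and a 2-year average delay

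*Protocol article*

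**What the plan says.** **The claim.** The Discussion states that "the 1-year follow-up after treatment will allow us to predict which patients are at risk of late radiation cystitis", and adds that these patients can be guided to radioprotective treatment. The Abstract's Conclusions carry the same claim. Neither place qualifies it.

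**The objective.** Under Exploratory Objectives, late cystitis appears only as something whose severity markers will be described. Participants' Calendar also calls it exploratory, and sets the aim as to "determine biomarkers that may be predictive of late radiation cystitis by quantifying biomarkers at week 52".

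**Frequency and timing.** Background and Rationale says that "in 5%-10% of cases, complications appear later (more than 6 months after radiotherapy". Participants' Calendar says that "the average delay in the occurrence of these complications is 2 years", and that late manifestations "may occur after a minimum of 3 months or even several years after the end of irradiation".

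**Follow-up.** The section on monitoring with the Cureety platform makes week 52 the end-of-study visit. End Points and Evaluation places the late assessment of cystitis symptoms and severity at week 52.

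**Size.** Statistical Analysis gives "a sample size of 60 individuals", says that "the sample size was not based on a statistical argument", and splits the sample on the hypothesis that "half of the patients initially included will develop cystitis".

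**The concern.** The article promises a prediction with a consequence for patient care, while its objectives promise only a description. Prediction needs enough patients who develop the outcome within follow-up, and markers measured before that outcome. The article's rate, delay and last visit leave very few late cases to learn from. The one sentence that says when the predictive markers are measured puts them at the visit where the outcome is recorded. Week-52 markers could predict only later onset, and no follow-up after week 52 is described.

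If the sentences stand, the final report could present a risk marker, and a reason to steer patients to treatment, that rests on a handful of events or on none.

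**Working it through.** **Inputs from the article:** N = 60, early cystitis 50%, two-sided α = 5% and power 80% (Statistical Analysis); late rate 5%-10% (Background and Rationale); mean delay 2 years (Participants' Calendar); last visit week 52; 33 markers (End Points and Evaluation).

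**1. The plan's own figure.** 60 × 0.50 = 30, so the 30/30 split reproduces. It rests on early cystitis alone. The late rate played no part in the sample size.

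**2. Late cases ever.** 60 × 0.05 = 3 and 60 × 0.10 = 6. These are expected numbers with no limit on follow-up, and need no assumption about onset.

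**3. Late cases by 1 year.** Expected number = 60 × rate × F(1), where F(1) is the share of late cases with onset within 1 year. The article gives only the mean, so the shape of F is assumed. Every shape below has mean 2 years. The chance of no case is (1 − rate × F(1))^60.

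| Assumed onset distribution | F(1) | Cases at 5% | Cases at 10% | Chance of none, 5% / 10% |
|---|---|---|---|---|
| Uniform, 0.5 to 3.5 years | 0.167 | 0.5 | 1.0 | 0.61 / 0.36 |
| Gamma, shape 2 | 0.264 | 0.8 | 1.6 | 0.45 / 0.20 |
| Exponential after 6 months | 0.283 | 0.9 | 1.7 | 0.42 / 0.18 |
| Lognormal, log-SD 0.8 | 0.320 | 1.0 | 1.9 | 0.38 / 0.14 |
| Exponential after 3 months | 0.349 | 1.0 | 2.1 | 0.35 / 0.12 |
| Exponential | 0.393 | 1.2 | 2.4 | 0.30 / 0.09 |
| Lognormal, log-SD 1.2 (median 0.97 years) | 0.509 | 1.5 | 3.1 | 0.21 / 0.04 |

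The range is about 0.5 to 3 cases. The origin of week 52 is not explicit. If it counts from the start of irradiation, the time since the end of treatment is shorter. Taking that time as 0.83 year (an assumption), the uniform shape gives 0.3 cases at the 5% rate.

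**4. What so few cases can show.** The two-group normal approximation gives the detectable difference in SD units as (z for α + z for power) × √(1/e + 1/(60 − e)), where e is the number of late cases. The sum of the two z values is 1.960 + 0.842 = 2.802 for one marker. With Bonferroni over 33 markers (α = 0.05/33 = 0.0015) it is 3.172 + 0.842 = 4.013.

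| Late v not late | √(1/e + 1/(60 − e)) | One marker | Bonferroni, 33 markers |
|---|---|---|---|
| 6 v 54 | 0.430 | 1.21 SD | 1.73 SD |
| 3 v 57 | 0.592 | 1.66 SD | 2.38 SD |
| 2 v 58 | 0.719 | 2.01 SD | 2.89 SD |
| 30 v 30 (early split, for scale) | 0.258 | 0.72 SD | 1.04 SD |

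At 6 v 54, power for a 0.8 SD difference in one marker is 46%; at 2 v 58 it is 20%. If there were 2 late cases and a rule flagged both, the exact lower 95% limit for its sensitivity would be √0.025 = 16%.

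**5. Timing, side by side.** Participants' Calendar quantifies the predictive markers at week 52. End Points and Evaluation assesses late symptoms at week 52. The Abstract's Methods give the last sample as week 48 instead. On either date no later outcome is described. Samples before irradiation and at weeks 4 and 12 do precede the week-52 assessment.

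**6. Definition of late.** Background and Rationale and Exploratory Objectives use more than 6 months. Participants' Calendar gives a minimum of 3 months.

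**The case against.** **The claim is outlook wording in an exploratory pilot.** The objectives are modest, the sample size is openly non-statistical, and no prediction model for late cystitis is specified. That is true, and it is why the fix is mainly rewording. It does not excuse two unqualified sentences that go beyond the objectives.

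**The power figures test an analysis the plan does not describe.** The objective concerns severity, and week 52 yields graded measures on all patients, so a split into late and not late is this review's construction. This stands in part. The figures are a yardstick for the claim of telling apart those at risk, not a forecast of the planned analysis.

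**A few cases by 1 year depends on an assumed shape.** This stands. A reader might infer from the 2-year mean that most men who develop late cystitis will count as unaffected at week 52. A mean does not fix the median: in the most skewed shape tried, about half have onset by 1 year. The argument therefore rests on the 3 to 6 cases ever.

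**The article does not say that late symptoms will be compared only with week-52 markers.** This also stands. A reader might infer a purely cross-sectional analysis, but no such comparison is stated, earlier samples exist, and the list of week-52 assessments in End Points and Evaluation omits the 33 markers. The fault lies in how the aim is worded, not in the data collected.

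**Sparse questionnaires.** A reader might also infer that the gap between weeks 12 and 52 hides most late episodes. The article calls hemorrhagic cystitis chronic as well as recurrent, so how many would be missed cannot be derived. Extra questionnaires would need an amendment to a study already under way and would not cure the shortage of events.

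**Conclusion.** The point holds against the claim of prediction and of guiding treatment in the Abstract's Conclusions and the Discussion. It does not touch the primary end point.

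The decisive figure, 3 to 6 expected late cases ever among 60 patients, follows from the article's own rate and size. Even with all 6 seen within follow-up, only differences of about 1.2 SD in one marker, or about 1.7 SD after correction for 33, are detectable with 80% power. The narrower figure of about 0.5 to 3 cases by 1 year rests on assumed onset distributions with mean 2 years. The detectable differences rest on a two-group normal approximation, full follow-up of all 60 patients, and Bonferroni correction as one possible adjustment.

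The timing in Participants' Calendar is a second, smaller fault, which the samples already planned can mend. The two statements on when late cystitis begins are an inconsistency to reconcile. With late symptoms assessed only at week 52, it hardly changes who is counted.

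**What to change.** 1. In the Abstract's Conclusions and the Discussion, replace the sentences on prediction and treatment with wording that matches the exploratory objective. For example: *The 1-year follow-up will describe biological markers and urinary symptoms at 1 year; no prediction of late cystitis and no guidance of treatment will be claimed from it.*
2. In Participants' Calendar, name the baseline, week-4 and week-12 markers as the candidate explanatory variables for week-52 symptoms. State that this analysis is hypothesis-generating, and treat week-52 markers as concurrent with the outcome. The shortage of late cases applies to this analysis too, so it should be reported as estimates with confidence intervals.
3. Reconcile the two statements on the onset of late cystitis (more than 6 months; a minimum of 3 months) and use one throughout. In the same pass, align the last sampling visit (week 48 or week 52).

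The change needs no new visits, samples or questionnaires. Its cost is a few edited sentences and a more modest stated conclusion.
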